## 2. STUDY DESIGN

The study is a randomized double-blinded cross-over trial, that will be carried out at the Leiden University Medical Center (LUMC) (Figure 3). This trial encompasses one screening day, of approximately 1 hour, and two study days, both with a duration of approximately 3.5 hours.

[figure not shown]

Figure 3 The study is a randomized double-blinded cross-over trial, encompassing one screening day and two study days. IV=intravenous; PO=per oral.

### 3. STUDY POPULATION

#### 3.1 Population (base)

The study will be carried out in 10 healthy white Caucasian men between 18 and 35 years old. Only young, male subjects will be included to ensure comparability with a currently performed parallel study of our collaborator dr. [name] (Université de Sherbrooke, Québec, Canada) who will use the same inclusion criteria. In addition, this will increase comparability with previously performed studies investigating the stimulation of the adrenergic receptors in human BAT activation [11, 20, 23]. Only white Caucasian subjects will be included in this study to enhance homogeneity of the study population, since BAT volume and activity was shown to differ between ethnicities [24]. In case of positive results, the study population should in future studies be expanded with females, other ethnicities or different ranges of BMI, to confirm applicability to the general population. All subjects will be recruited via advertising at the LUMC and in university buildings in Leiden. In addition social media, such as Facebook and LinkedIn, and the website of the Dutch Heart Foundation will be used to advertise.

#### 3.2 Inclusion criteria

To be eligible to participate in this study, a subject must meet all the following criteria:

- White Caucasian males
- Age between 18-35 years old
- Lean ( $BMI \geq 18$  and  $\leq 25 \text{ kg/m}^2$ )

#### 3.3 Exclusion criteria

A potential subject who meets any of the following criteria will be excluded from participation in this study:

- Diabetes mellitus (determined on basis of fasting glucose levels defined by ADA criteria)
- Any other active endocrine disease (thyroid disease, any signs of Cushing's syndrome, adrenal disease and lipid-associated disorders such as familial hypercholesterolemia)
- Any cardiac disease (i.e. ischemic cardiac disease, arrhythmias, severe heart failure)
- A first-degree family member with sudden cardiac death
- Any chronic renal or hepatic disease
- Use of beta-adrenergic receptor agonists (for e.g. asthma)
- Use of medication known to influence glucose and/or lipid metabolism or brown fat activity (e.g. beta-blockers, antidepressants, corticosteroids)
- Use of medication shown to increase risk on hypokalemia after salbutamol administration (e.g. xanthine derivatives, steroids and diuretics)

- Any other contra-indications for the use of salbutamol or propranolol
- Abuse of alcohol or other substances
- Smoking
- Participation in an intensive weight-loss program or vigorous exercise program during the last year before the start of the study
- Current participation in another research projects that may influence the current research project
- Participation in another research with exposure to radiation burden within a year before the start of the current study
- Clinically relevant abnormalities in clinical chemistry or electrocardiogram (ECG) at screening (to be judged by the study physician)

### 3.4 Sample size calculation

For this study the main outcome parameter is net glucose uptake by BAT after administration of salbutamol, as measured by dynamic  $^{18}\text{F}$ -FDG PET-CT scan.

Our sample size calculation is based on the results recently published by Blondin et al.[1] and Orava et al. [25]. Blondin et al. showed net glucose uptake by BAT as measured by dynamic  $^{18}\text{F}$ -FDG PET/CT after administration of the maximal allowable dose mirabegron (200 mg) of  $22 \pm 14$  nmol/g/min. We expect the effect of salbutamol on glucose uptake by BAT to be at least as big as the effect of the maximal allowable dose mirabegron. Orava et al. [25] showed net glucose uptake by BAT in thermoneutral condition of  $9 \pm 4$  nmol/g/min. Therefore, we predict the net glucose uptake of salbutamol in combination with propranolol to be comparable to the net glucose uptake by BAT in thermoneutral condition. Thus, we consider a difference in net glucose uptake by BAT of  $+13$  nmol/g/min after salbutamol administration as clinically relevant, with a SD of 10,  $\alpha = 0.01$ ,  $\beta = 80\%$ . Based on these parameters we need 10 subjects (<http://biomath.info/power/prt.htm>; based on Snedecor & Cochran, Statistical methods 7th edition).

In case a subject is withdrawn from the study before finishing all measurements, the investigator will try finding a replacement to maintain the initial population size.

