### 9.1 Primary study parameter

Our primary study parameter is glucose uptake by BAT, as measured by dynamic [ $^{18}\text{F}$ ]FDG PET acquisition. Patlak graphical analysis method [43] will be used to determine the fractional extraction of [ $^{18}\text{F}$ ]FDG ( $K_i$ ) in BAT

([http://www.turkupetcentre.net/petanalysis/model\\_patlak\\_interpretation.html](http://www.turkupetcentre.net/petanalysis/model_patlak_interpretation.html)). Patlak analysis will be based on the plasma input curve (time-radioactivity curve from the aorta), the BAT time-radioactivity curve, and the time in which [ $^{18}\text{F}$ ]FDG has reached steady-state in BAT (approximately 8-10 minutes). Based in the  $K_i$  we will calculate metabolic rate of glucose (MRglu).

$\text{MRglu} = (\text{Glucose concentration in plasma} / \text{Lumped constant}) * K_i$ .

(Lumped constant = 1.14 for adipose tissue)

- Differences between the effect of salbutamol in combination with placebo, and salbutamol in combination with propranolol will be assessed by paired-sample t-test or Mann-Whitney test.

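### The planning SD of 10 is the lower bound that the two cited SDs (14 and 4) allow for a paired difference, so 10 subjects give the stated 80% power at alpha 0.01 only at a very high within-subject correlation, if at all.

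*Protocol*

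**What the plan says.** Section 3.4 takes two results from the literature. The first is BAT glucose uptake "after administration of the maximal allowable dose mirabegron (200 mg) of" 22 ± 14 nmol/g/min, which stands in for salbutamol with placebo. The second is 9 ± 4 nmol/g/min under thermoneutral conditions, which stands in for salbutamol with propranolol. Subtracting the means gives the target difference of 13, which the section calls relevant "after salbutamol administration as clinically relevant, with a SD of 10". Alpha is 0.01, and the 80% is printed as β. The section concludes: "Based on these parameters we need 10 subjects". It cites a web calculator based on a standard textbook.

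The design is a cross-over, and section 9.1 says that the treatment difference "will be assessed by paired-sample t-test or Mann-Whitney test". Section 3.4 does not say whether the test is one- or two-sided, whether 10 is the SD of the paired difference, or how 10 was obtained. There is no allowance for dropout; instead, "the investigator will try finding a replacement to maintain the initial population size".

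**The concern.** A paired t-test is powered on the SD of the within-subject difference. That SD depends on the two marginal SDs and on the correlation between a man's two scan days. The section quotes both marginal SDs and then uses a third figure, 10, without derivation. That figure equals 14 − 4, the smallest value the two SDs can produce. Planning on it amounts to assuming that each man's propranolol-day uptake is an exact increasing linear function of his placebo-day uptake. Any weaker relation gives a larger SD and lower power.

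This is the only power statement for the primary endpoint. If it is too high, readers of the protocol and of the result will think the trial better able to detect a difference of 13 than it is.

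**Working it through.** **Inputs, all from section 3.4.** Difference d = 22 − 9 = 13; marginal SDs 14 and 4; planning SD 10; alpha 0.01; power 80%; n = 10. The correlation r is not given, so a range is an assumption. Sidedness is not given, so both are shown.

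**Step 1: reproduce the plan's figure.** For a paired comparison, n = ((z for alpha + z for power) × SD / d)². Two-sided at 0.01 with SD 10:

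(2.576 + 0.842)² × (10/13)² = 6.9

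Adding 2 for the small sample gives 8.9, so 9. Adding z²/2 instead (2.576²/2 = 3.3) gives 10.2, so 11. The exact non-central t calculation gives 11 two-sided and 9 one-sided. The stated 10 lies within this spread, so the sample size follows from an SD of 10. The question is the SD itself.

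**Step 2: the SD of the paired difference.**

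SD_diff = sqrt(14² + 4² − 2 × r × 14 × 4) = sqrt(212 − 112r)

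Setting SD_diff = 10 gives r = (212 − 100)/112 = 1.00. No admissible r gives a smaller value.

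**Step 3: exact paired-t power**, with n = 10, 9 degrees of freedom and non-centrality 13 × sqrt(10)/SD_diff.

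| r | SD_diff | Power, two-sided 0.01 | Power, one-sided 0.01 | n for 80%, two-sided |
|---|---|---|---|---|
| 1.0 | 10.00 | 77.7% | 87.3% | 11 |
| 0.9 | 10.55 | 72.4% | 83.3% | 12 |
| 0.8 | 11.06 | 67.4% | 79.2% | 12 |
| 0.7 | 11.56 | 62.7% | 75.3% | 13 |
| 0.5 | 12.49 | 54.5% | 67.8% | 15 |
| 0.3 | 13.36 | 47.7% | 61.2% | 16 |
| 0 | 14.56 | 39.7% | 52.9% | 19 |

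**Step 4: where 80% is reached.** With 10 subjects, two-sided alpha 0.01 and 80% power, the standardised difference must be 1.332. The SD may then be at most 13/1.332 = 9.76, which is below the lower bound of 10. One-sided, the SD may be up to 10.97, so r must be at least (212 − 10.97²)/112 = 0.82.

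**Step 5: detectable difference** at 80% power, two-sided 0.01: 1.332 × 12.49 = 16.6 at r = 0.5, and 1.332 × 14.56 = 19.4 at r = 0, against the planned 13.

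**Step 6: rounding.** The SDs are printed as whole numbers. With 13.5 and 4.5 the lower bound falls to 9.0, and two-sided power there is 86.9%. Reaching an SD of 9.76 with those values needs r = (13.5² + 4.5² − 9.76²)/(2 × 13.5 × 4.5) = 0.88. A very high correlation is still required.

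**The case against.** Several points on the other side stand.

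- **The arithmetic from SD 10 to 10 subjects is sound.** The two-sided gap at SD 10 is one subject (11 against 10), which is the difference between an approximation and the exact t. A reader might infer a calculation error, but the weakness lies in the SD that was entered.
- **Sidedness is open.** A reader might infer that 80% is out of reach at any correlation. That holds only for a two-sided test with the SDs taken exactly as printed. A one-sided test reaches 80% from r of about 0.82, and rounding could move the two-sided bound.
- **Every correlation is an assumption.** The SDs come from two separate studies and may not be those of this trial, so 54.5% and 39.7% are scenarios. Section 3.4 does not say that 10 was derived from 14 and 4. The root mean square of the two, sqrt((196 + 16)/2) = 10.3, is another possible origin, but it equals the paired SD only at r = 106/112, about 0.95.
- **The shortfall depends on the strict alpha.** At two-sided 0.05 power is 83% at r = 0.5 and 71% at r = 0. Section 3.4 also expects salbutamol to do at least as well as mirabegron, so 13 is meant as a minimum. Neither point rescues the stated claim, which is for 13 at 0.01.

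Three stronger readings are not supported. Printing β = 80% does not mean the trial was planned at 20% power: about 10 subjects follow only if 80% is the power, so it is a labelling slip. That section 9 does not repeat alpha 0.01 is not a fault, since an analysis plan may fix it. Nor does the protocol set any rule by which a null result would count against the ADRB2 hypothesis, so such misuse is speculation.

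**Conclusion.** The point holds as a defect in the power justification. With the cited SDs as printed, an SD of 10 is the most favourable value possible and requires perfect within-subject correlation, for which the protocol offers no basis. Two-sided at 0.01, 10 subjects give 77.7% power at best, and 62.7% to 39.7% for r from 0.7 down to 0. One-sided, the range runs from 87.3% at r = 1 to 52.9% at r = 0.

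These figures assume normally distributed differences, a true difference of 13, and the cited SDs carrying over to this trial. All the scenarios point the same way: the stated 80% needs a very high correlation under either sidedness. The paired design and the type I error of the paired t-test are unaffected.

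**What to change.** Keep 10 subjects and rewrite the power statement in section 3.4 so that it gives:

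1. the SD of the within-subject difference, with its source or the assumed correlation range (for r from 0.7 to 0, SD 11.6 to 14.6);
2. whether alpha 0.01 is one- or two-sided;
3. 1−β = 80% in place of β = 80%;
4. the power range that 10 subjects give, or the difference detectable with 80% power (two-sided: 16.6 at r = 0.5, 19.4 at r = 0).

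The cost is a less favourable stated power. No subjects, scans or radiation are added.

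Analysing log(MRglu) may be added as a prespecified sensitivity analysis. It should not be presented as a free replacement for the primary test. Under lognormal data with the cited moments, its power at 0.01 is 92% at r = 0.5 but 63% at r = 0, so the gain rests on the distribution and on r. It also turns the target from a difference of 13 nmol/g/min into a ratio. Switching to a signed-rank test whenever a value is not positive would make the choice of test depend on the data.

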#### 4. TREATMENT OF SUBJECTS

This is a randomized double-blind cross-over trial in young healthy men. For all subjects the intervention consists of IV injection of salbutamol in combination with placebo and, as comparator, IV injection of salbutamol in combination with propranolol, in random order. In addition, at both study days all subjects will undergo a low-dose dynamic  $^{18}\text{F}$ -FDG PET/CT scan.

##### 4.1 Investigational product

The investigational product in this study is salbutamol. During the two study days subjects will receive a single-dose of 250 µg salbutamol via IV injection over a time-course of 5 minutes. Salbutamol is a selective ADRB2 agonist approved for the symptomatic treatment of asthma and chronic obstructive pulmonary disease (COPD) [26]. More information on salbutamol will be included in the following section 'Investigational product'.

Administration of salbutamol will be given in combination with placebo (study day A) or in combination with 80 mg propranolol (study day B) (Figure 3 and 4). Placebo and propranolol will be given orally in two capsules 60 minutes prior to salbutamol injection and are solely used to further elucidate which receptors are involved in the working mechanism of salbutamol on human BAT. Therefore, placebo and propranolol are not considered investigational products. More information about placebo and propranolol will be provided in section 7 'Non-investigational product'.

##### 4.2 Use of co-intervention

Not applicable

##### 4.3 Escape medication

Not applicable

## 5. INVESTIGATIONAL PRODUCT

### 5.1 Name and description of investigational product

In this study subjects will receive a single dose of 250 µg salbutamol by IV injection over the time-course of 5 minutes on both study days to investigate the effect of salbutamol on glucose uptake by human BAT. Salbutamol is a selective ADRB2 agonist used for the prevention and symptomatic treatment of bronchospasms in asthma and chronic obstructive pulmonary disease (COPD). Administration of salbutamol in IV form is approved in clinic for the acute treatment of severe asthmatic attacks and status asthmaticus[27]. Our study protocol is based on a study recently performed by Kruizinga et al. [28] in the Centre for Human Drug Research (CHDR) in Leiden. In this study, IV salbutamol in a dosage of 500 µg was proven to be safe and well-tolerated. Salbutamol will be provided by the LUMC department Clinical Pharmacy and Toxicology.

### 5.2 Summary of findings from preclinical studies

The rationale of this study is based on extended preclinical and clinical research showing that BAT is most potently activated through the sympathetic nervous system, which acts via adrenergic receptors present in adipose tissue. This research shows that in rodents ADRB3 mRNA is predominantly found in high levels in brown adipocytes [10]. Directly targeting the ADRB3 using CL316243, one of the most selective ADRB3 agonists available, was shown to effectively activate BAT and improve cardiometabolic outcomes [8, 9]. More specifically, activation of the ADRB3 reduces plasma triglyceride and cholesterol levels, decreases body weight and consequently attenuates atherosclerosis development [8]. The potential benefit of activating BAT via stimulation of adrenergic receptors is thus clearly illustrated in preclinical research. However, in human studies directly targeting the ADRB3 has thus far led to inconsistent results [11, 12, 20]. In addition, a recent study shows that human BAT shows negligible expression of ADRB3 with abundant expression of ADRB2[1]. Therefore, in this study we aim to investigate the effect of selectively targeting the ADRB2 using salbutamol. Preclinical studies investigating the effect of salbutamol on brown adipose tissue are scarce, due to the low expression of the ADRB2 in rodent BAT. One study showed no direct effect of salbutamol on brown adipocytes, but an increased glucose uptake by BAT in mice due to increased blood flow through the tissue [29]. In addition, a recent study investigated exclusively peripheral stimulation of the ADRB2, using PEGyAMPH. They showed increased sympathetic outflow towards WAT and BAT, leading to increased lipolysis and thermogenesis [30]. Altogether, it is very plausible that, while in mice the ADRB3 is the most important adrenergic receptor for the activation of BAT, in humans the ADRB2 in fact activates BAT. Other non-clinical studies investigating the selective stimulation of the ADRB2 with salbutamol or other

compounds mainly focused on pulmonary and cardiovascular outcomes and will therefore not be summarized here. For findings from preclinical studies regarding pharmacological safety of salbutamol we refer to the 'Summary of Product Characteristics' (SPC), which can be found on the website of the 'College ter Beoordeling van Geneesmiddelen' (CBG) (<https://www.geneesmiddeleninformatiebank.nl/nl/>, registration number RVG 07686) and to the product specification in appendix D2.

### 5.3 Summary of findings from clinical studies

Salbutamol is approved in clinical care since 1968 for the prevention and treatment of bronchospasms in asthma and chronic obstructive pulmonary disease (COPD) and is thus extensively studied regarding cardiopulmonary outcomes. A few studies have focused on the effect of salbutamol on energy metabolism [13-15, 31]. However, none of them specifically focused on human BAT.

The ADRB2 is one of the three subtypes of beta-adrenergic receptors, which are well-acknowledged to be important for the regulation of energy metabolism [32]. Several studies showed that selective stimulation of the ADRB2 using IV administration of salbutamol, with or without blocking the ADRB1 using atenolol, increases energy expenditure, lipid oxidation and lipolysis [13-15, 31]. This effect appears to be lower in obese compared to lean subjects [13] and is possibly affected by different polymorphisms of the ADRB2 [15]. These results are in line with our hypothesis that specifically stimulation of the ADRB2 will lead to increased activation of human BAT, which in turn leads to increased energy expenditure, lipid oxidation and lipolysis.

### 5.4 Summary of known and potential risks and benefits

Findings from clinical studies regarding pharmacological safety and potential adverse effects of salbutamol can be found in the 'Summary of Product Characteristics' (SPC), which can be found on the website of the 'College ter Beoordeling van Geneesmiddelen' (CBG) (<https://www.geneesmiddeleninformatiebank.nl/nl/>, registration number RVG 07686) and in the product specification in appendix D2. In addition, a structured risk analysis can be found in paragraph 13 'Structured risk analyses'. We will here discuss the main side effects of concern and the precautions we will be undertaking. At all times there will be a medical doctor and nurse present during the study days. The study protocol regarding the route of administration of salbutamol and the to be undertaken precautions is based on a study recently performed by Kruizinga et al. [28] at the Centre for Human Drug Research (CHDR) in Leiden.

#### *Cardiovascular side effects*

Sympathomimetic drugs such as salbutamol can induce cardiovascular effects, often

(>10%) including tachycardia and palpitations and rarely (0.01-0.1%) including arrhythmias [26]. This could potentially be a risk for patients suffering from ischemic cardiac disease, arrhythmias or severe heart failure. Therefore, we screen all subjects on cardiac abnormalities using an ECG during the first screening visit. In addition, family history regarding cardiac diseases or sudden death will be interrogated. In case of any cardiac abnormalities subjects will be excluded for participation in this study. In addition, during the study day we will monitor heart rate and blood pressure using a cuff connected to a digital blood pressure device at three set time points (at the start of the study day, before administration of salbutamol and after PET/CT scan), and we will monitor heart rate and rhythm during PET/CT scan using a 3-lead ECG connected to a bedside patient monitor. Before administration of salbutamol we accept a heart rate < 100 beats per minute and a systolic blood pressure <140 mmHg. Previously performed studies in healthy subjects report a mean increase of ca. 15 heart beats per minute after continuous IV salbutamol administration (50-100 ng/kg fat free mass per minute) [13, 15]. In this study we will administer salbutamol intravenously via a single bolus. We expect the initial increase in heart rate to be comparable to the rates mentioned in the aforementioned studies and we expect this to decline over-time to baseline levels after administration [33].

#### *Hypokalemia*

Hypokalemia may occur after IV administration of salbutamol, an effect that is potentiated by hypoxia and concomitant treatment with xanthine derivatives, steroids and diuretics [26]. In this study we will only include healthy subjects that are not suffering from bronchospasms and are thus not hypoxic. In addition, we will exclude subjects that use one of the aforementioned drugs. During the screening visit, at the start of the study day and at the end of the study day we will monitor serum potassium levels.

#### *Lactic acidosis*

Lactic acidosis has very rarely (<0.01%) been reported after administration of high doses of IV salbutamol [26]. High levels of lactate could lead to dyspnea and compensatory hyperventilation and Kussmaul breathing. Therefore, study physicians will be aware of any signs of dyspnea (e.g. tachypnoea). However, the occurrence of lactic acidosis seems unlikely in our study design in which we only inject a single dose of salbutamol, since acidosis is shown to quickly resolve after reduction or termination of salbutamol administration [34].

## 5.5 Description and justification of route of administration and dosage

In this study we will administer 250 µg salbutamol via an IV single dose injection over 5 minutes.

Salbutamol is available and approved for clinical use in inhalation, intramuscular, subcutaneous and IV form. Salbutamol inhalation is most commonly used in clinic and particularly works locally in the bronchopulmonary tract. However, in this study we are interested in the effect of salbutamol on BAT activation. Only a small proportion of the administered dose after inhalation will enter the blood stream [28, 35], and is thus able to cause an effect in adipose tissue. In addition, the variability in inhalation techniques causes variable plasma concentrations of the drug after inhalation [28]. This high variability in plasma concentrations between subjects could lead to an inconsistency in pharmacological activity at the effect site. Salbutamol by IV injection or infusion is approved for the symptomatic treatment of severe asthmatic attacks or status asthmaticus, in a minimum dose of 250 µg or 5 µg/min IV respectively [26]. Previously performed studies investigating the effect of salbutamol on energy metabolism have all used IV administration of salbutamol [13-15, 28, 31]. After IV administration plasma concentrations appear to be rather consistent [28]. Kruizinga et al. [28] used a single dose injection of 250 µg and 500 µg salbutamol in their study protocol and did not experience severe side effects. Almost all subjects became moderate tachycardic which lasted for around 30 minutes, however, subjects were informed about this beforehand and none of them experienced this as highly uncomfortable. In the previous section (6.4 Summary of known and potential risks and benefits) we summarized the potential risks and the precautions we will be undertaking to limit potential risks to a minimum.

